#### Secondary analyses

To assess predictors of effects, steps of a study on predictors of change during CBT for chronic pain will be followed [59]. Pain interference at 3-month follow-up will be used as indicator of treatment effect. Using the PROCESS macro for SPSS [60], linear regression models will be applied (two-tailed). Predictor variables may include sex, age, educational level, number of comorbidities, time since CIPN onset, CIPN symptom severity (EORTC QLQ – CIPN20), quality of life (EORTC QLQ-C30), pain intensity (NRS), psychological distress (HADS), psychological inflexibility (PIPS), mindfulness (FMI-NL), valued based living (ELS), and pain catastrophizing (PCS). They will be selected based on theoretical and empirical considerations.

To assess differences in effects between the guided and unguided version of the intervention, independent samples t-tests and a two-stage hierarchical multiple regression analysis for each primary and secondary outcome will be conducted. Baseline to 3-month follow-up change will be used as the dependent variable. The independent variable will be an intervention dummy variable. Baseline score on the respective outcome measure will be used as control variable. Effect sizes for both conditions will be computed to indicate differences in the magnitude of the effects of online ACT with and without email counseling.

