### Sample size calculation

Per group, 51 participants during follow-up measurements are necessary to detect minimal effect sizes of interest (*d* = .50) on the primary outcome. This is based on earlier findings on effectiveness of online and face-to-face ACT intervention for chronic pain [33, 34]. The power will be high enough (*p* = 1-beta = .80) to find significant effects in a two-sided test at alpha = .05. As found in previous online ACT interventions, a drop-out rate of 30% needs to be considered. G*Power calculations revealed that 73 participants per group are needed at baseline, which means that 146 participants are needed in total.

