### Statistical analysis

#### Primary analyses

Significant differences at baseline between the conditions will be checked by performing one-way ANOVA’s and chi-square tests.

Effects of the intervention on all outcomes will be assessed by performing intention-to-treat analyses using general linear mixed models. Baseline to post-intervention and 3- and 6-month follow-up differences will be used as repeated measures, with treatment (2 levels), time (3 levels) and their first-order interactions as fixed factors. Confidence intervals of 95% will be calculated for all outcomes. Drop-out and non-adherence are relatively common in online interventions [56]. Therefore, secondary analyses will be performed to examine effects on outcome variables for participants who adhered to the intervention (i.e., all session completed and self-reported minimum of 2 h per week spent on intervention). At post-intervention and follow-up, effect sizes (Cohen’s *d*) will be calculated using means and standard deviations. Effect sizes of 0.80 are considered large, effect sizes of 0.50 are evaluated as moderate, and effect sizes of 0.20 are considered small [57].

Initiative on Methods, Measurement, and Pain Assessment in Clinical Trials (IMMPACT) recommendations will be followed to evaluate the proportion of participants showing clinically significant change [58]. Clinical improvement will be assessed with missing values imputed by the Expectation Maximization-algorithm. Proportions of clinically improved participants and Chi-square tests will assess statistically significant differences in the proportions for the two conditions. It will be calculated for (a) pain interference (MPI – Interference), (b) pain intensity (NRS), and (c) CIPN symptom severity (EORTC QLQ – CIPN 20). A decrease of at least 0.6 standard deviation will be assessed as evidence of clinically significant change for the MPI – Interference scale, based on the IMMPACT guidelines [58]. Decreases of 20% or higher in pain intensity (NRS) will be assessed as minimum and moderate changes. No specific IMMPACT guidelines exist for the HADS. Therefore, a distribution-based decrease of at least 1 standard error of the mean is recommended [58].

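### The moderator analysis (Objective 2) uses a single-visit regression at 3 months that ignores post-intervention scores of participants without a 3-month score, although the planned mixed model would use them

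*Protocol article*

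**What the plan says.** The Background section of the protocol article sets three objectives, the second being to find baseline factors that moderate the effect. Under Statistical analysis, Secondary analyses, the outcome for this is pain interference at the 3-month follow-up (T4), and the method is stated as: "Using the PROCESS macro for SPSS [60], linear regression models will be applied (two-tailed". Baseline pain interference is not among the candidate predictors listed there. A baseline control variable is named only for the guided-versus-unguided comparison.

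Primary analyses handles effects on all outcomes differently, by "performing intention-to-treat analyses using general linear mixed models", with the changes from baseline to post-intervention (T3), 3 months (T4) and 6 months (T5) as repeated measures. It names one missing-data method, Expectation Maximization imputation, and only for the proportions with clinical improvement. It also remarks that drop-out and non-adherence are relatively common in online interventions.

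Sample size calculation says that "a drop-out rate of 30% needs to be considered" and plans 73 per group, 146 in total.

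For Objective 3, Secondary analyses states: "Baseline to 3-month follow-up change will be used as the dependent variable".

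**The concern.** The same section of the plan holds two ways of treating a participant who answers at T3 and then stops. The Objective 1 model keeps that T3 score. The Objective 2 regression has no place for it.

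Two things are at stake. One is precision, which is already scarce for interaction terms. The other is bias: if people who do poorly at T3 are more likely to be missing at T4, those left for the regression are a selected group. The arm contrast is then distorted when the selection differs between arms, and the interaction can be distorted even when it does not. Selection that differs by arm is plausible here, because only the ACT arm carries a course of about 2 hours a week, while the waiting list is waiting for access.

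**Working it through.** **1. The plan's own figures.** The drop-out step reproduces: 51 / (1 − 0.30) = 72.9, so 73 per group and 2 × 73 = 146. If the same 30% were missing at T4 and nothing were imputed, the regression would lose 146 × 0.30 = 43.8, about 44 people, and keep about 102. This is a ceiling that rests on those two conditions. (The 51 itself does not follow from the stated two-sided inputs: an exact t calculation gives 64, and 51 is the one-sided number. That is a separate matter and nothing below depends on it.)

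**2. What each method takes from a participant, given a baseline score.**

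| Scores after baseline | Regression at T4 | Mixed model over T3, T4, T5 |
|---|---|---|
| T3 and T4 | used | used |
| T3 or T5, not T4 | nothing | used |
| none | nothing | nothing |

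Only the middle row separates the methods, so the mixed model recovers part of the 44, not necessarily all.

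**3. Arm contrast by simulation.** From the protocol: 73 per arm, 30% without T4 in each arm, effect 0.50 SD. Assumed, because the protocol gives none: correlations 0.6 (baseline–T3), 0.6 (baseline–T4) and 0.7 (T3–T4), T3 complete, and the drop-out mechanism. Effects are shown as positive for benefit.

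| T4 drop-out | Baseline-adjusted regression | Likelihood model using T3 |
|---|---|---|
| Random in both arms | 0.50 | 0.50 |
| Worst 30% at T3 leave, both arms | 0.50 | 0.50 |
| ACT: selection weight doubles per SD of worse T3; WLC random | 0.58 | 0.50 |
| ACT: worst 30% at T3 all leave; WLC random | 0.69 | 0.50 |

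- Bias in the third row: 0.58 − 0.50 = 0.08 SD. If instead the odds of leaving double per SD, the adjusted regression gives 0.56. With equal correlations of 0.5 or 0.7 it gives 0.54 to 0.55.
- In the third row the unadjusted T4 score gives 0.63 to 0.66, and a change score gives 0.52.
- Under random drop-out the SD of the arm estimate is 0.160 (adjusted regression) against 0.154 (likelihood).

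**4. Moderator term, the target of Objective 2.**

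- Standard error of the interaction: about 0.16 (0.163 in one set of runs) baseline-adjusted, against 0.157 to 0.158 in the likelihood model. 0.163 / 0.158 = 1.03, about 3% wider.
- On the unadjusted T4 score the standard error is about 0.20. 0.20 / 0.157 = 1.27, but most of that gap (0.20 to 0.16) comes from adding the baseline score, not from recovering T3.
- When drop-out follows T3 in both arms, a true interaction of 0.30 is estimated as 0.27 to 0.29, a bias of 0.01 (adjusted) to 0.03 (unadjusted).

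**5. Where the mixed model does not help.** If drop-out in the ACT arm follows the unseen T4 score, large-sample runs with equal correlations of 0.5 to 0.7 give 0.60 to 0.65 for the adjusted regression and 0.58 to 0.64 for an estimate using T3. Both are biased.

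**The case against.** The strongest reply is that the article nowhere says participants without a 3-month score are deleted. Regression can be run on imputed data, the team plans imputation elsewhere, and missing-data handling for secondary analyses is often left to a SAP or full protocol, neither of which is shown. This stands as far as it goes: silence on missing data is not the point. What remains is a choice the article does make, namely a single-visit method, when a model that uses the other visits is already planned a few paragraphs earlier. The one imputation method named is tied to a different analysis.

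A reader might also infer three stronger things that the documents do not support:

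- **That intention-to-treat is abandoned.** Nothing in Secondary analyses has anyone analysed other than as assigned. The difference lies in the use of partial follow-up.
- **That 30% of those randomised will be lost.** The 30% is a planning rate for follow-up in general, not tied to T4 or to an arm.
- **That the result will be biased.** That depends on the drop-out mechanism. Random drop-out gives none, and equal T3-driven drop-out gives none in the arm contrast.

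It is also fair to say that the gain for Objective 2 is small in the scenarios tried. A much smaller standard error, 0.130, can be had by averaging T3 and T4, but that estimates something other than the planned 3-month effect and is not counted here.

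**Conclusion.** The point holds for Objective 2 and is modest in size. As described, the moderator regression takes nothing from participants with a T3 but no T4 score, up to about 44 of 146 if the planning rate applied at T4 without imputation. Under the assumed correlations the cost is about 3% in the standard error of a baseline-adjusted interaction and a bias of 0.01 to 0.03 in an interaction of 0.30 when drop-out follows T3. It is about 0.08 SD in the baseline-adjusted arm contrast when it does so in the ACT arm only, and more under extreme selection. These figures assume T3 is complete, which favours the mixed model.

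A reader might extend the point to Objective 3 and replace its t-tests and regression with the Objective 1 arm contrast. The documents do not support that. Waiting list condition offers the unguided course only at 5 months (T4), which Study design makes the 3-month follow-up. The waiting-list change up to T4 therefore contains no unguided course, and the Objective 1 contrast would simply repeat ACT against waiting list. A 3-month follow-up after an 8-week unguided course would fall at about 5 + 2 + 3 = 10 months, beyond the 8 months of participation.

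**What to change.** Estimate moderation in the Objective 1 mixed model, on all randomised participants with any post-baseline score. Add arm x moderator x visit terms with their lower-order terms and the baseline pain interference score, treat visit as categorical, and read out the arm x moderator contrast at 3 months, so that the planned estimand is unchanged. Keep the PROCESS regression as a sensitivity analysis.

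The cost is a change of wording in the analysis plan and slightly more modelling; results no longer come straight from PROCESS output. No new data are needed. The change relies on data missing at random given the observed scores and does not solve drop-out that depends on the unseen 3-month score.

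For Objective 3, do not substitute the Objective 1 arm contrast. Study design, Waiting list condition and Secondary analyses must first be reconciled on when the unguided course is taken and which change is to be compared. The analysis set and method can be settled after that.

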Even though online interventions are relatively new, several such interventions have demonstrable effectivity in improving QoL in cancer patients and survivors [28, 30–32]. A randomized controlled trial (RCT) has shown that the use of an online CBT intervention significantly improved CIPN pain intensity and may be effective [27]. Furthermore, research has shown that online interventions based on ACT are capable of improving pain intensity, pain interference, pain catastrophizing, disability, depression, anxiety, psychological inflexibility, and QoL in chronic pain patients with a variety of pain diagnoses (e.g., fibromyalgia, rheumatoid arthritis, and back complaints) [33, 34]. These findings suggest that an online self-help intervention based on ACT might be effective for adult cancer survivors with chronic painful CIPN as well. However, effects may differ between patients, since previous research has shown factors such as pain intensity, depressive and anxiety symptoms, and emotional well-being to predict the effectiveness of online ACT for chronic pain [35], and the extent to which patients benefit from the online intervention may hence vary. Furthermore, there may also be differences in the effectiveness with different types of the online intervention, namely with or without guidance. Earlier research has shown that guidance, including feedback, explanations, motivations and reminders, improves treatment effects compared to unguided interventions [36, 37]. The primary aim of this study researching the online intervention named ‘Embrace Pain’ is to reduce pain interference in cancer survivors with chronic painful CIPN. To study this, three objectives have been formulated:*Objective 1:* To examine the effectiveness of an online self-help intervention based on ACT for reducing pain interference in cancer survivors with chronic painful CIPN in a randomized controlled trial (RCT) and compare this to a waiting list condition (WLC).*Objective 2:* To examine which baseline demographic, clinical, and psychosocial factors may moderate the effectiveness of an online self-help intervention based on ACT.*Objective 3:* To examine the extent to which effects differ between guided and unguided versions of the online self-help intervention based on ACT.

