## Methods

### Study design

An RCT will be carried out with two parallel, non-blinded groups. Participants will be involved in the study for a duration of 8 months from the first to the last measurement. Outcome measures will be collected at baseline (T0), early-intervention (T1; 3 weeks after baseline), mid-intervention (T2; 6 weeks after baseline), directly at the end of intervention (T3; 2 months after baseline), and through two follow-up measurements (T4; 3 months after the intervention, T5; 6 months after intervention). A flowchart of the study is shown in Fig. 1.

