### Waiting list condition

The control condition includes a WLC. At 5 months after start (i.e., T4) participants in the WLC receive the opportunity to follow the intervention without email guidance by a therapist. They neither receive a welcome letter at the start, which means that they only read the introduction about the training before starting.

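### The guided-versus-unguided analysis uses a follow-up at which nobody has yet taken the unguided course, so as written it cannot answer Objective 3

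*Protocol article*

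**What the plan says.** Objective 3 in the Background of the Protocol article is: "To examine the extent to which effects differ between guided and unguided versions of the online self-help intervention based on ACT". Under Randomization there are two arms only, guided ACT and WLC. The unguided course exists solely as what the WLC is offered later: "At 5 months after start (i.e., T4) participants in the WLC receive the opportunity to follow the intervention without email guidance by a therapist".

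Study design fixes the clock. The guided course ends at T3 ("directly at the end of intervention (T3; 2 months after baseline"), followed by "two follow-up measurements (T4; 3 months after the intervention, T5; 6 months after intervention". Participation lasts 8 months from first to last measurement.

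The analysis for Objective 3 is under Secondary analyses: "To assess differences in effects between the guided and unguided version of the intervention, independent samples t-tests" and a two-stage hierarchical regression, for each primary and secondary outcome. On the outcome variable it says: "Baseline to 3-month follow-up change will be used as the dependent variable". The predictor is an intervention dummy and the baseline score is the covariate. No separate baseline or follow-up is defined for the WLC's later course.

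**The concern.** The outcome window closes at the moment the unguided course opens. In the WLC, change from T0 to T4 is change while waiting. The dummy would be labelled guided versus unguided, but it would estimate guided ACT versus no course. That is the same contrast, at the same time point, as the 3-month term of the primary mixed model.

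A real benefit of ACT over waiting would then be reported as a benefit of email guidance. The Background already cites research in which guidance improves effects, so a result in that direction might not be questioned.

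**Working it through.** **Timeline, from Study design, Intervention and Waiting list condition**

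- T3, end of the guided course: month 2.
- T4 = 2 + 3 = month 5. This reproduces the protocol's own equation of T4 with 5 months after start.
- T5 = 2 + 6 = month 8, the last measurement. This agrees with the stated 8-month total.
- Unguided course: opens at month 5 and lasts 8 weeks (56 / 30.44 = 1.84 months), so it ends at about month 6.8.
- Unguided exposure in the WLC at T4 = 5 − 5 = 0 months.

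**Can another reading supply an unguided 3-month outcome?**

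| Reading for the WLC | Window | Result |
|---|---|---|
| As written | T0 to T4, months 0 to 5 | No unguided exposure |
| 3 months after the unguided course ends | about 5 + 2 + 3 = month 10 | About 2 months after the last measurement |
| Clock reset at T4 | T4 to T5, months 5 to 8 | Exists, but is not stated and does not match |

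On the third reading, WLC T5 falls 3 months after course start and 8 − 6.84 = about 1.2 months after course end. Guided T4 falls 5 months after course start and 3 months after course end.

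**Size of the error if the analysis is run as written**

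Inputs from Sample size calculation: d = 0.50, 51 per group at follow-up, two-sided alpha 0.05. Two inputs are assumptions: guidance adds nothing, and the baseline-to-follow-up correlation r, which the protocol does not give, lies between 0.3 and 0.7. SDs are taken as equal at both times.

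- Change-score t-test: the variance of change is 2(1 − r) in SD² units, so the standardised difference is 0.5 / √(2(1 − r)), with 100 degrees of freedom.
- Baseline-adjusted regression: the residual variance is 1 − r², so the standardised difference is 0.5 / √(1 − r²), with 99 degrees of freedom.
- Noncentrality = standardised difference × √(51/2); power is from the noncentral t distribution.

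| r | Change score: difference | Probability | Regression: difference | Probability |
|---|---|---|---|---|
| 0.3 | 0.423 | 0.56 | 0.524 | 0.75 |
| 0.5 | 0.500 | 0.71 | 0.577 | 0.82 |
| 0.7 | 0.645 | 0.90 | 0.700 | 0.94 |

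With no guidance effect, a valid two-sided test would reject with probability 0.05. Virtually all of the rejections in the table favour guided.

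**The case against.** The strongest reply is that the authors mean condition-specific time points: for the WLC, T4 as baseline and T5 as the 3-month measurement. T5 is exactly 3 months after access. The same section says that effect sizes will show the magnitude of ACT with and without email counselling, which makes sense only if the WLC's change covers its course. So a reader who infers that the trial holds no unguided outcome at all goes too far: T5 is one. But the section does not state this reset, and with it the two arms would still be measured at different distances from course end.

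A reader might also object that the comparison is not randomised, because unguided users are those who stayed and took up the offer. That does not apply to the analysis as written, since T0-to-T4 change in the two full arms is the randomised contrast. It applies once post-T4 data are used, and so belongs with the remedy.

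Fig. 1 and Table 2 are not shown and could hold WLC-specific assessments, but the 8-month total in the text leaves no room for one after month 8.

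Finally, this is a secondary analysis, and analysts might notice the problem before mislabelling a waiting period. That lowers the chance of a wrong report but does not make the stated rule correct.

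**Conclusion.** Wrong as written. The specified outcome window contains no unguided treatment, so the planned tests cannot answer Objective 3. This is not detail left to an analysis plan: the article itself fixes the dependent variable, predictor, covariate and tests, and the fault lies in what it fixes.

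The error probabilities (0.56 to 0.90 for the t-test, 0.75 to 0.94 for the regression) illustrate the size. They hold if the text is followed literally, ACT beats waiting by the protocol's minimal effect of interest, guidance adds nothing, and r lies in the assumed range. The timeline conclusion needs none of these assumptions.

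A reader might infer that Objective 1 is damaged too. The documents do not support that on this point: the month-2 and month-5 comparisons of ACT with waiting are not affected by this defect.

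**What to change.** Rewrite the Objective 3 paragraph under Secondary analyses as follows.

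- Unguided effect: change from T4 to T5 in WLC members who start the course.
- Guided comparator: change from T0 to T3, with T0 to T4 as a sensitivity analysis. At 2 and 5 months after course start, these bracket the WLC's 3 months.
- Apply the same course-starter restriction in both arms. Restricting only the WLC would leave non-starters in the guided arm and could favour unguided.
- Adjust for the score at course start: T0 in the guided arm, T4 in the WLC.
- State that the comparison is non-randomised and exploratory, that follow-up is unequal, that unguided users are self-selected, and that only the guided arm receives a welcome letter, so guidance is not the only difference.

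Dropping the unadjusted t-test in favour of the regression is optional.

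Cost: analysis wording only. T4 and T5 are already in the schedule; the article does not show that the data have been collected. The downside is that Objective 3 becomes an explicitly exploratory, short-term comparison.

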#### Interview analyses

Qualitative data will be used to gain further insight in the intervention effects, usage, usability, content fit of intervention with complaints, and satisfaction. All interviews will be recorded and transcribed verbatim. Thematic analysis in Atlas Ti 8.0 will be used to analyze the data. Following transcription, two researchers will independently (re)read a set of 3–4 interviews and perform inductive coding followed by a discussion of disparities. One researcher will further code the rest of the interviews using a codebook that will be generated from the first round of coding, adding new codes along the way, and discussing outcomes of coding with the second researcher.

